### 1.3. Research Objectives

The overarching goal is to provide a scientific foundation for devising brain-directed and evidence-based treatments in children and adolescents with MLD. Based on insights from recent empirical research, this study addresses at least five gaps in research:(1)Examining the long-term safety and feasibility of a multisession tRNS protocol in the pediatric population (e.g., 10 sessions);(2)Determining the effects of the tRNS setup (over bilateral dlPFCs vs. bilateral PPCs) in improving long-lasting arithmetic learning and performance and neuropsychological and psychological measures compared with sham tRNS;(3)Testing whether and the extent to which arithmetic improvements after tRNS are related to neuropsychological changes;(4)Understanding whether and the extent to which changes in spontaneous EEG after tRNS are linked to arithmetic improvements;(5)Assessing whether and the extent to which improvements in arithmetic performance correlate with changes in the psychological function of children and their parents’ stress.

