Parents are asked to read each item (e.g., “Did he/she look angry or lose his temper?”) and indicate how much or how often the child has exhibited specific symptoms in the last two weeks on a five-point Likert scale from 0 (“Absent or not at all”) to 4 (“Severe or almost every day”). Items that are related to suicidal ideation, suicide attempts, and use of substances are answered “Yes”, “No”, or “I don’t know”. Consistently high scores in a particular domain might indicate significant and problematic symptoms for the participant, which could justify further evaluation, treatment, and follow-up.

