#### 2.5.6. Safety and Tolerability

Symptoms and side effects will be assessed using a standard questionnaire [89] to be completed by participants after each session and at each follow-up (T1, T2, and T3). The questionnaire lists adverse effects, such as headache, neck pain, scalp pain, tingling, itching, burning sensation, skin redness, sleepiness, trouble concentrating, and acute mood change. Participants will quantify the intensity of the symptoms or side effects that are related to tRNS as follows: (1) absent; (2) mild; (3) moderate; and (4) severe.

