### 2.7. Safety Considerations

There are minimal risks that are associated with participation in the study. The potential risks are as follows: (1)Transcranial random noise stimulation. Considering the paucity of safety data on tRNS, this technique is considered safe, as supported by a recent study in juvenile mice [61]. Previous studies [90,91] have shown that tRNS with the current intensity that we use here is less likely to be perceivable. Compared with tDCS, tRNS has the advantage of having higher cutaneous perception thresholds and lower response rates [90]. Adverse effects will be registered throughout the study. The experimenter will also follow participants for adverse effects after the end of the study.(2)Cognitive training/assessment. There is a risk that participants will find the tasks to be challenging, fatiguing, or boring. Should this occur, participants can take a break at any time or can discontinue the testing. Research staff will explain what to do and how to perform the tasks during study visits.

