## 4. Discussion

We have described the rationale and design of a trial that aims to determine whether tRNS, combined with cognitive training, will have a clinically meaningful impact on math and math-related (e.g., working memory, mental rotation) abilities and psychological and neurophysiological measures in children and adolescents with MLD. This study will constitute the first attempt to prove the safety and feasibility of multiple (e.g., 10 sessions) and consecutive sessions of tRNS in the pediatric population. In addition, the project will determine the most effective placement of tRNS electrodes (Frontal vs. Parietal) compared with placebo (Sham) in terms of behavioral and neurophysiological long-term improvement. The results will represent a significant step toward clinical translation in the field.

A unique facet of this study relies on the potential synergy of multitarget interventions, with one each serving as “endogenous” activation, targeting behavior through cognitive training, and “exogenous” neuromodulation [55] through its direct neurophysiological effect on brain regions that surround the electrodes on distal cortical areas. Accordingly, tRNS would act to desynchronize pathological cortical rhythms via enhancing the neural signals detection and thus improving the neural processing and the related behavior [58,60,97]. In our case, tRNS has the potential to prompt math training-induced neuroplasticity, facilitating brain activity in the frontal or parietal network during cognitive training.

An additional unique feature is that our study will involve repeated consecutive sessions of tRNS combined with cognitive training as multiple sessions of transcranial electrical stimulation gave higher chances of cumulative biological effects over time [98]. The decision of a multi-sessions protocol was made after cautiously considering neurophysiological and preliminary data that supported evidence for tolerability and safety of this technique in children at this stage [66,99,100]. In line with our considerations, a recent study [73] applied five-days of tRNS combined with cognitive training in children with attention deficit hyperactivity disorder and the authors revealed no clinical-meaningful side effects or related safety-issues at any follow-up.

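### The first objective is long-term safety, but the only specified safety instrument mainly covers acute stimulation effects, and a non-significant chi-square at three months says little about lasting harm

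*Protocol article*

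**What the plan says.** Section 1.3 puts safety first among the aims: "Examining the long-term safety and feasibility of a multisession tRNS protocol in the pediatric population". The Discussion (section 4) goes further: "This study will constitute the first attempt to prove the safety and feasibility of multiple (e.g., 10 sessions) and consecutive sessions of tRNS".

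Section 2.5.6 specifies one instrument, a standard questionnaire that the child completes after every session and again at T1, T2 and T3. On its content it says: "The questionnaire lists adverse effects, such as headache, neck pain, scalp pain, tingling, itching, burning sensation, skin redness, sleepiness, trouble concentrating, and acute mood change". On the rating it says: "Participants will quantify the intensity of the symptoms or side effects that are related to tRNS as follows", followed by four grades from absent to severe.

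Section 3.2 compares the safety measures between groups by chi-square, and section 3.3 expects the three groups not to differ on them.

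Other information on harm appears elsewhere. Section 2.7 states: "Adverse effects will be registered throughout the study", and adds that follow-up for adverse effects continues after the study ends. Section 2.5.4 describes a parent-rated sleep scale and a 25-item psychiatric symptom scale. Of the latter it says: "Consistently high scores in a particular domain might indicate significant and problematic symptoms for the participant". Section 2.5 schedules the outcome measures at T0, T1, T2 and T3. Sections 3.2 and 3.3 treat the psychological measures as secondary outcomes in mixed models, with improvement expected.

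**The concern.** The objective and the measure do not match. Most of the listed items arise at the electrode or during the session. The rating is limited to symptoms that the child relates to tRNS. At T3 a blinded child must therefore link a present symptom to stimulation that ended three months before. A new sleep or mood problem could easily go unreported under that condition.

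The measures better suited to showing a lasting adverse change are collected at the same visits but are not classed as safety. The general adverse-effect records are not tied to the objective either. The stated route to a safety conclusion is thus a chi-square on the questionnaire, with no difference as the hoped-for result. In a trial of this size such a result is likely whether or not there is moderate harm, and the Discussion's wording invites a reader to take it as evidence of safety.

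**Working it through.** **Inputs from the protocol article**
- Last session Day 12, T2 Day 19, T3 Day 102 (section 2.3). T2 is 19 − 12 = 7 days and T3 is 102 − 12 = 90 days after the last stimulation.
- 34 recruited and 26 evaluable per group, 30% dropout, f = 0.15, α = 0.05, 80% power (section 2.6).

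**The plan's own figure.** For the group-by-time interaction, λ = f²·N·m/(1 − ρ) = 0.0225 × 78 × 4/0.5 = 14.04, with 6 and 225 degrees of freedom. Power is 0.801, so 78 is reproduced (ρ = 0.5 and sphericity are assumed; the article states neither). The size was set for a continuous repeated measure. No safety precision enters it.

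**What zero events would exclude.** The exact one-sided 95% upper bound is 1 − 0.05^(1/n).

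| Children in the arm | Upper bound |
|---|---|
| 34 (all recruited) | 8.4% |
| 26 (planned evaluable) | 10.9% |
| 24 (34 × 0.70 = 23.8) | 11.7% |

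Under section 2.9, children who withdraw or are removed stop all study assessments, so the lower rows are the realistic ones for T3.

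**What a non-significant comparison means.** This is a pairwise normal approximation to the planned test: power = Φ[(|p₁ − p₂| − 1.96·SE₀)/SE₁], with SE₀ = √(2p̄(1 − p̄)/n) and SE₁ = √((p₁q₁ + p₂q₂)/n). The event rates are assumed, because the article gives none.
- 20% against 5%, n = 26: SE₀ = 0.0917, SE₁ = 0.0893, power 0.37 (0.46 at n = 34).
- 10% against 2%, n = 26: SE₀ = 0.0659, SE₁ = 0.0649, power 0.22 (0.28 at n = 34).

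A fourfold or fivefold excess would be missed more often than found.

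**Would the mixed models show it instead?** Suppose 5 of 34 children in an arm worsen by 1 SD and the rest do not change. The arm mean moves 5/34 = 0.147 SD. The standard error of an arm contrast is √((2/34)(1 − r²)): 0.210 SD at r = 0.5 and 0.173 SD at r = 0.7 (r assumed). The shift is smaller than one standard error.

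**Would counting 1 SD declines show it?** The change score has SD √(2(1 − r)), which is 1.00 at r = 0.5 and 0.77 at r = 0.7. With no harm, 16% or 10% of children pass 1 SD by chance, or 5.4 or 3.3 of 34. In the same scenario the expected count is 29 × 0.159 + 5 × 0.5 = 7.1, or 29 × 0.098 + 5 × 0.5 = 5.4. The excess is about 2 children, so a raw 1 SD count is no better than the mean contrast.

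**The case against.** The strongest reply is that the plan captures more than the questionnaire, and that an article leaves the tabulation of adverse events to documents not shown. Much of this stands.

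- Adverse effects are registered during the study and followed afterwards (section 2.7), and section 2.3 provides for serious adverse events in the unblinding rule. A reader might infer that the questionnaire is the only safety capture. It is not; it is the only instrument that the article specifies.
- The item list is illustrative, and headache, sleepiness and trouble concentrating can persist. A reader might infer that T3 must look clean by construction. The documents do not establish that.
- A reader might infer that the other scales serve only to show benefit. That is wrong for the psychiatric symptom scale, which has no stated direction of improvement and whose high scores may prompt further evaluation of the individual child. The BDE-2 Number Line subtest is the primary outcome, and nothing makes the mixed models one-sided, so mean worsening would be visible.

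What does not stand is the appeal to unseen documents. The article itself states the objective, the instrument, the test, the expected result and the intended claim, and these do not fit together. An individual clinical flag protects the child concerned, but it does not enter the stated safety comparison.

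**Conclusion.** The concern holds in a limited form. The plan specifies no safety outcome suited to lasting harm at T3, and it does not assign the measures and records that could inform the first objective to that objective. As written, the safety conclusion rests on a non-significant chi-square on mainly acute, attribution-limited items. Per active arm, even a result with no events leaves true rates up to 8.4% (34 children) or 10.9% (26 children) compatible with the data at one-sided 95% confidence.

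These bounds are exact and assume only independent children and complete ascertainment. The power figures rest on assumed event rates, and the mean-shift and count figures on assumed correlations of 0.5 to 0.7.

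A reader might pool the two active arms and quote 4.3% (68 children) or 5.6% (52 children). That bound applies only if the two montages share one risk, which a trial designed to compare them should not presume. Nor do the documents show that harm will be missed or that the trial is unsafe. The point is what a null result could support. It should be corrected, but it does not undermine the efficacy comparison.

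**What to change.** 1. Name as long-term safety outcomes the T2 and T3 changes from T0 on the psychiatric symptom scale and the sleep scale, worsening on N-back and BDE-2, and the adverse-effect records of section 2.7.
2. Report each active arm against sham with confidence intervals for the difference. Add counts of children who deteriorate beyond a prespecified reliable-change or clinical-range threshold, read against the sham count. Do not use a raw 1 SD change.
3. Keep the questionnaire as the tolerability measure. Base the safety conclusion on exact per-arm intervals and not on a non-significant chi-square.
4. In the Discussion, replace the claim of proving safety with the event rate that the trial can exclude per arm, about 8 to 11% if no events are seen.

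The scales and records are already planned, so the cost is a few extra tables and a less favourable safety statement. Counts will still be small, which is why the intervals should carry the conclusion.

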### 2.6. Sample Size Considerations

The sample size was calculated by a priori analysis in G * Power, version 3.1.9.7 (The G*Power Team, Düsseldorf, Germany).

Because the design of this project has never been employed in children and adolescents with MLD, we could refer only to a pilot study that determined the effects of tRNS, combined with cognitive training, in children with MLD [66]. However, the study included 12 children with a medium effect size but differs in several aspects from ours: the number of tRNS sessions, number of groups, and cognitive training. To be conservative and start from these premises, we calculated the expected effect size (f) to low and estimated it at 0.15.

With an estimated f = 0.15, α value = 0.05 (i.e., probability of false positives of 5%), and β = 0.80 (i.e., at least 80% power), the sample size that was required for repeated-measures analysis of variance (RM ANOVA) with 3 groups (Frontal Group vs. Parietal Group vs. Sham Group) and 4 measurements (T0 vs. T1 vs. T2 vs. T3) was 78 (i.e., 26 per group). Considering a 30% dropout rate in the follow-ups, we will plan to recruit a total of 102 participants (i.e., 34 per group).

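### Section 2.6 applies the 30% dropout allowance as 78 × 1.3 instead of 78 / 0.7, so 102 recruits leave about 71 completers, fewer than the 78 its own calculation requires

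*Protocol article*

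**What the plan says.** Section 2.6 (Sample Size Considerations) gives the inputs as "With an estimated f = 0.15, α value = 0.05 (i.e., probability of false positives of 5%), and β = 0.80 (i.e., at least 80% power". The symbol β is used for power there, but the gloss makes the meaning clear. The number needed for a repeated-measures ANOVA with three arms and four visits "was 78 (i.e., 26 per group". The recruitment target follows in the next sentence: "Considering a 30% dropout rate in the follow-ups, we will plan to recruit a total of 102 participants (i.e., 34 per group".

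Three other places bear on the point:

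- Section 3.2 plans linear mixed-effects models for the primary and secondary outcomes and gives their handling of missing values as one reason.
- Section 2.9 says that participants who withdraw stop all study assessments.
- Section 3.3 expects the benefit to appear at T1 and to persist at T3.

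**The concern.** The required number, the dropout rate and the recruitment target stand next to each other and do not fit together. A 30% dropout rate means that 30% of those recruited are lost, so the required number has to be divided by 0.7. The plan multiplied it by 1.3, which adds 30% of the smaller number and gives too few.

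The recruitment target and the only power statement in the document both depend on this step. If dropout reaches the rate the plan expects, the trial ends with fewer completers than its own calculation calls for, and a reader of section 2.6 would not know it.

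**Working it through.** **Inputs from section 2.6:** f = 0.15; α = 0.05; power 0.80; k = 3 groups; m = 4 measurements; required N = 78; dropout 30%; target 102 (34 per group).

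**Assumed, not stated:** correlation among repeated measures ρ = 0.5 and nonsphericity correction ε = 1.

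**1. Reproduce the 78.** For the group-by-time interaction, λ = f² × N × m × ε / (1 − ρ), df1 = (k − 1)(m − 1) = 6 and df2 = (N − k)(m − 1).

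- N = 78: λ = 0.0225 × 78 × 4 / 0.5 = 14.04, df2 = 225, power 0.801.
- N = 77: power 0.795.

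So 78 is the smallest number that reaches 80% under these settings, with no slack. Other readings of the test do not give 78: the within-subject main effect needs 63 and the between-group effect 273. The result is sensitive to ρ: ρ = 0.4 needs 93 and ρ = 0.6 needs 63.

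**2. Reproduce the 102.** 78 × 1.3 = 101.4, rounded up to 102. Per group, 26 × 1.3 = 33.8, rounded up to 34. Both match the document.

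**3. Apply the stated dropout to the target.** 102 × 0.7 = 71.4 completers; per group, 34 × 0.7 = 23.8 against 26.

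**4. The allowance that 30% implies.** 78 / 0.7 = 111.4, so 112. With equal arms, 26 / 0.7 = 37.1, so 38 per group and 114 in total; 114 × 0.7 = 79.8 completers.

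**5. The dropout that 102 does cover.** 1 − 78 / 102 = 0.235, or 23.5%.

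Steps 2 to 5 do not depend on ρ or ε.

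**6. Completer-only power in the sizing model (ρ = 0.5, ε = 1).**

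| Completers | Power |
|---|---|
| 78 | 0.801 |
| 72 | 0.761 |
| 71.4 | 0.757 |
| 71 | 0.754 |

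**7. Approximate power when all available data are used.** Assumptions: 34 recruited per arm, 30% lost in each arm, equal variances with a common correlation of 0.5, data missing at random, and an effect scaled so that 78 complete participants give 0.801. Power of the group-by-time test:

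| Shape of effect | Dropouts miss T3 only | Miss T2 and T3 | Leave after baseline |
|---|---|---|---|
| Present at T1, persists to T3 | 0.90 | 0.88 | 0.81 |
| Grows linearly over visits | 0.84 | 0.80 | 0.79 |
| Present at T3 only | 0.77 | 0.77 | 0.76 |

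**The case against.** The strongest reply is that the trial will not be analysed by a completers-only ANOVA. The mixed model in section 3.2 keeps the visits of participants who leave later. Section 2.6 places the dropout in the follow-ups, and section 2.5 lists T1 apart from the follow-ups T2 and T3, so a typical dropout may still contribute T0 and T1. (Section 2.5.6 counts T1 among the follow-ups, so this reading is natural but not certain.) For an effect that appears at T1 and persists, the pattern expected in section 3.3, the table in step 7 shows power of 0.81 to 0.90 with 102 recruits and 30% loss.

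That reply stands as far as power is concerned. A reader might infer from the arithmetic that the trial cannot deliver its stated 80% power, or that power at 30% dropout is simply about 75%. The documents support neither. The 75% belongs to the completers-only ANOVA used for sizing and rests on ρ and ε values that the document does not give.

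The reply does not rescue the sentence. Section 2.6 does not use the mixed model to justify 102. It takes an ANOVA requirement of 78 and adds an allowance for dropout, and a 30% allowance on 78 is not 102. Reading the 30% as a margin of extra recruits would fit the multiplication, but the text calls it a dropout rate. The mixed model also does not remove the loss in every case: for an effect seen only at T3, power stays at about 0.76 to 0.77.

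**Conclusion.** The inflation in section 2.6 is wrong as written. The target is 10 below the total that 30% dropout requires (112), or 12 below with equal arms (114). At the plan's own rate, about 71 completers remain where 78 are required, and 102 is sufficient only up to 23.5% dropout. These statements need no assumption.

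The consequence for power is smaller and conditional. In the sizing model, with ρ = 0.5 and ε = 1 assumed, completer-only power is about 0.75–0.76 instead of 0.80. Under the planned mixed model it is about 0.76 to 0.90, given the assumptions in step 7. The error biases no result and changes no analysis. It makes the recruitment target inconsistent with the requirement and dropout rate stated beside it.

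**What to change.** Correct the sentence in section 2.6 in one of two ways:

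- Keep 102 and state that it preserves the required 78 completers up to 23.5% dropout. If a power figure at 30% dropout is added, give it as about 75%, label it as completer-only repeated-measures ANOVA power, and state the ρ and ε behind it.
- Keep 102 and justify it with a power calculation for the mixed model in section 3.2 under 30% dropout, stating the assumed correlation, the timing of dropout and the shape of the effect.

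The first costs one sentence. The second costs one sentence and a short calculation. Neither needs extra participants.

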### 2.7. Safety Considerations

There are minimal risks that are associated with participation in the study. The potential risks are as follows: (1)Transcranial random noise stimulation. Considering the paucity of safety data on tRNS, this technique is considered safe, as supported by a recent study in juvenile mice [61]. Previous studies [90,91] have shown that tRNS with the current intensity that we use here is less likely to be perceivable. Compared with tDCS, tRNS has the advantage of having higher cutaneous perception thresholds and lower response rates [90]. Adverse effects will be registered throughout the study. The experimenter will also follow participants for adverse effects after the end of the study.(2)Cognitive training/assessment. There is a risk that participants will find the tasks to be challenging, fatiguing, or boring. Should this occur, participants can take a break at any time or can discontinue the testing. Research staff will explain what to do and how to perform the tasks during study visits.

### 2.8. Protection of Risks

To minimize any risk that is associated with tRNS, participants will be monitored throughout the stimulation sessions and asked to report any discomfort. If the scalp sensation is uncomfortable, the stimulation will be stopped. In the event of a headache, the stimulation will be stopped. All tRNS sessions will be administered and supervised continuously by a trained experimenter. There are no reports of seizures having been induced by tRNS in human participants. However, to avoid any chance of seizure, a prior history of neurological disorders is an exclusionary criterion for our study, and no participants will have a history of seizure. The risks that are associated with cognitive training and assessment are minimal. Nevertheless, breaks will be offered if participants experience frustration with the tasks.

